#### Self-Efficacy to Complete Mammography

A single item ("how confident are you that you can complete breast cancer screening?") [8] will be combined with a four-item scale that showed excellent internal consistency (alpha = 0.82) and factor loadings from 0.65-0.68 in a confirmatory factor analysis [56].

#### Prior Breast Cancer Screening Test Utilization

Participants will be asked if they have ever been screened for breast cancer and how long ago the test was received. This nine-item set of questions has been used in pilot studies by the research team [50] and was adapted from Behavioral Risk Factor Surveillance System questions. This set of questions will also ask whether or not a participant has undergone any breast cancer testing for diagnostic purposes.

#### Cancer Fatalism

We will employ an adapted Powe Cancer Fatalism inventory to evaluate beliefs toward early detection, treatment, and cancer myths (10 questions).

#### Implementation Intentions - only delivered to **MI**^**2 **^participants

Implementation intentions measures have been adapted from the work of Gollwitzer and Sheeran, et al [30,39]. To assess Pre-Action/Pre-contemplation Implementation Intentions, participants will be asked where, when, and how they will seek out more information on breast cancer prevention ("do you think you will try to get more information about breast cancer?" "Do you believe you will talk to any of the following individuals about breast cancer prevention?" "Can you pin down a date you think you will first talk to this person about breast cancer prevention? ___/____/______"). For Action/Contemplation Implementation Intentions, participants will be asked specific action-oriented questions regarding mammography. A participant who describes an intention to complete screening mammography may also be asked (among other things) to set a specific date they plan to be screened, whether they need to get a healthcare provider referral, what mammography facility they will call to set up their appointment (the telephone number will be supplied to participants automatically by the HLK-BH program once a facility is selected).

##### Process Evaluation

It is necessary to document and analyze the process of program implementation to verify the integrity of the intervention, allow for correction of problems as they occur, provide data to examine the relationship between program delivery and program outcomes, and to guide future investigations [57-59]. Therefore, a comprehensive set of process assessments, including both qualitative and quantitative data, will be designed or adapted from previous studies to measure implementation, participation, and fidelity.

We plan to measure characteristics of the participants and community health and environmental issues that may influence breast cancer screenings. In addition, we will collect information that may provide useful insight into refining protocols and materials. Another aim of the evaluation is to provide a general description of the context in which the intervention is conducted. Table 4 summarizes the variables to be measured and the data collection instruments to be used.

**Table 4 T4:** Summary of Process Evaluation Measures

Source	Instruments	Variables of Interest
Participants	HLK-BH program; 120 day follow-up telephone call	Demographics, ease of use of notebook computer, type of insurance coverage (i.e., Medicare, uninsured, commercial), new/emerging illness, benefits/barriers (# of miles to screening facility), discomfort with screening procedure

Community Health Workers	CHW training session tracking form; attendance records	Attendance at training sessions, turnover, transfers, level of support for program (e.g., importance of breast cancer screenings)

External and competing programs	Indian Health Service & United Methodist Mexican American Ministries Clinic Director questionnaire	Programs/Information/Policies designed to increase breast cancer screenings not initiated by us

#### Community Participants

We will assess the ability of the participants to use the notebook computer by direct observation and follow-up with questions regarding the ease of use during our planned exit survey. In addition to demographic characteristics, we will collect type of insurance coverage, which has been found to have a differential effect on cancer screenings [60]. The Community Health Workers will perform these observations. We will also determine if screening rates could be affected by dominant mammography facilities distributed asymmetrically across our target communities [61], number of miles to screening mammography facilities, and level of perceived discomfort with screening procedure, etc. To identify issues related to perceived benefits and challenges, we will ask a subsample of participants about the helpfulness, relevance, convenience, level of satisfaction, etc. of their Healthy Living Kansas-Breast Health program Community Health Worker. Measuring participant's satisfaction and soliciting information about potential benefits and barriers will provide valuable feedback about the extent to which the activities have met with patient expectations [62]. We will use structured interviews to be completed during the end of the study to determine benefits and barriers, helpfulness of Community Health Workers, why they did or did not get screened, and whether or not they would recommend the program to others. These random assessments will be conducted via telephone for 10% of participants.

#### Community Health Workers

The quality and integrity of the HLK-BH program will be partially dependent on how the CWHs carry out the education and recruitment sessions. The ability of the CHW to conduct activities consistent with program goals will vary across workers. This variation will be related to a number of factors including training, self-efficacy, number of years experience, understanding of the overall program, and level of perceived support. We will administer a training workshop survey to the CHWs during the training session to document their attendance and their level of support for and importance of the HLK-BH screening program. Further, we will assess the CHW's level of confidence to implement the research protocol as designed. In addition, we will track turnover and/or transfer rates to document potential study personnel issues and track CHW participation in weekly group teleconference calls, encrypted data transfers, and recruitment logs. We will assess these factors by administering a questionnaire to all CHWs involved in the study.

#### HLK-BH Components

We will use a number of different strategies to document the degree to which the research protocol was implemented as planned. For example, each notebook computer or HLK-BH Internet program will track the amount of time to complete the HLK-BH assessment. We will also assess the number of individuals who were ineligible for the intervention program because they self-reported being in compliance with screening guidelines, already had a screening appointment scheduled, had an acute and/or terminal medical condition at the time of their recruitment interaction with a CHW.

#### External and Competing Programs

We will ask mammography facility personnel local to Mayetta and Garden City, KS to complete a short questionnaire to assess whether their facility received any breast cancer-related information not related to our project, which was shared with patients, or if promotional activities were conducted to increase breast cancer screenings, in addition to our research project during our study time period, which might serve to contaminate or lessen program effects. Information gained will be used to help us determine if external or competing factors might have influenced breast cancer screening objectives, posing as possible internal validity threats [63].

#### Process Evaluation Analysis

We have planned process evaluation procedures to provide detailed information regarding the intervention implementation. The process evaluation will include paper and pencil surveys, structured interviews, and monitoring logs to collect quantitative and qualitative data on specific program components and implementation issues. Monitoring the extent and quality of implementation will allow us to guard against "Type III Error" in which an intervention, not fully implemented as planned, is not a true test of the experimental hypotheses [64].

Descriptive statistics will be used to provide a general description of the context in which the intervention is being conducted (e.g., participant, CHW, and community recruitment setting characteristics). Individual characteristics, for example, may contribute to or detract from intervention effects. To monitor intervention components across recruitment communities and exposure to program elements, we will develop estimates of adherence rates from survey information and self-report measures, magnitude of intervention effects and the variability of outcome.

The content of comments from structured interviews completed by participants will be examined for common themes related to recommendations for improving training protocols and materials, and factors related to implementation of the screening program. Comments will be analyzed by employing the content analysis techniques recommended by Miles [65]. Identification of and suggestions for the removal of barriers to participation, and for procedures to enhance adherence will be summarized to allow for midcourse corrections in implementation, to refine the intervention design, and to provide direction to our intervention strategies [66].

### Study 3: Data Analysis and Dissemination

#### Data Analysis

Descriptive statistics will be generated from the sample using the demographic measures. Pearson's χ^2 ^test will be used to compare the proportions of categorical characteristics between the two intervention groups. The two-sample t-test will facilitate the comparison between the groups for characteristics measured on a continuous scale. This will allow us to evaluate the randomization, as we would expect to find roughly 5% of these findings to be statistically significant at the α = 0.05 level.

##### Aim #1

To compare the 120-day post randomization mammography screening completion rates of individuals who receive a computerized mammography "implementation intentions" (**MI**^**2**^) intervention, versus a comparison computerized condition of general breast cancer prevention health education (**C**).

For this aim, both the outcome (120-day post randomization breast cancer screening completion) and predictor (treatment group) are dichotomous, so a 2 × 2 table will be generated to compare the proportions of those completing screening between the **MI**^**2 **^versus **C **intervention groups. A χ^2 ^statistic will be used to test the null hypothesis of no difference in these proportions between these two [67]. The distribution of measured and unmeasured confounding variables (beyond community location) should be relatively balanced between the intervention groups due to the random assignment of the intervention within communities and participants. However, if serious imbalances are apparent from the descriptive statistics described above, we will use unconditional logistic regression to model this dichotomous outcome. Predictor variables will include the intervention group and the unbalanced demographic characteristics to reduce the impact of such biases. Indicator variables identifying the community will also be included to control for this stratification variable as described by Agresti [67]. The results of this logistic regression will be transformed into estimates of the proportion screened [68] adjusted for the potential confounding variables. The fit of the model will be assessed using the Deviance statistic and the Hosmer-Lemeshow goodness-of-fit test [68].

To measure the impact of attrition on the part of the study participant, a sensitivity analysis will be performed. This can be done using the methods described by Rothman and Greenland [69] by examining what the results would be under various assumed scenarios for those missing the outcome. This will include a conservative imputation approach which will assume that all of those for whom this outcome is unknown were not screened during the 120-day post randomization period.

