#### Design

This study will be a randomized trial that will evaluate the differential impact of the **MI**^**2 **^(intervention) and **C **(control) study arms on 120-day post randomization breast cancer screening utilization rates. Randomization will occur at the participant level. Women will be randomized to a treatment group within each community outreach recruitment event. This stratified random sampling design will minimize the variation between the **MI**^**2 **^and **C **intervention arms by allocating the variation between each Northeast and Southwest Kansas recruitment event to the strata parameters. In doing so, the variation between interventions will be minimized, much like a randomized complete block design.

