#### Sample Size and Sample Size Justification

This study will utilize Latina and AI/AN female participants from two distinct communities with approximately 121 randomized participants per community to test the main effects of the **MI**^**2 **^vs. **C **arms at 120 days post randomization. For this study, a total of 290 subjects will be randomized to either the **MI**^**2 **^or **C **treatment arms (to account for a possible 20% attrition rate from randomization to 120 day follow up). It is anticipated that 30% of those in the **MI**^**2 **^group will receive their breast cancer screening within the 120 day study period compared to 15% in the **C **group. A total of 242 subjects (121 per study arm) would have 80% power to detect the anticipated difference in screening rate between the **MI**^**2 **^and **C **groups at the α = 0.05 (two-sided) type I error rate (Table 5). Assuming up to a 20% attrition rate based on the research team's prior studies in rural Kansas, a total of 290 subjects will be randomized to either the **MI**^**2 **^or **C **treatment arms (145 per treatment). Additional screening rates were examined for study power (Table 5) to select an adequate sample size to detect clinically relevant differences. Numbers contained in Table 5 demonstrate that the sample will have at least 80% power to detect clinically relevant differences. Similar tables to Table 5 were also compared with varying sample sizes, with the final sample size selected being the choice that optimized both study power with the logistical constraints.

**Table 5 T5:** Power estimates (%) for a sample size of 121 subjects per group with α = 0.05 (two-sided)

		Breast Cancer Screening - Implementation Intentions	
		25%	30%
Breast Cancer Screening	10%	87	97
		
Controls	15%	Not Relevant	80

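### Women are randomised within recruitment event, but the Aim 1 test is an unstratified chi-square, and stratum terms enter only through an undefined imbalance trigger

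*Protocol article*

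**What the plan says.** The Design section of the protocol article randomises individual women within each community recruitment event. It says that this reduces variation between the arms by "allocating the variation between each Northeast and Southwest Kansas recruitment event to the strata parameters", and it likens the scheme to a randomised complete block design.

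Under Data Analysis, Aim #1, the primary comparison is a single 2 × 2 table of arm by 120-day screening completion. A chi-square "statistic will be used to test the null hypothesis of no difference in these proportions between these two" groups. No stratum enters this test.

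The same section adds a fallback: "if serious imbalances are apparent from the descriptive statistics described above, we will use unconditional logistic regression to model this dichotomous outcome". That model holds the intervention group, the unbalanced demographic characteristics and indicators for community. Recruitment event is not mentioned. No threshold is given for a serious imbalance.

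The descriptive statistics that feed the trigger are baseline comparisons by chi-square and t-test. The article says of these that "we would expect to find roughly 5% of these findings to be statistically significant" at the 0.05 level.

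Aim #3 repeats the conditional rule with a cumulative logit model and community indicators. Aim #2 is looser: extra predictors can be added by multiple regression if imbalance is serious, and no stratum term is named.

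**The concern.** Stratifying the randomisation balances the arms within events. The gain in precision reaches the p-value only if the analysis conditions on the strata. A pooled chi-square charges the between-event variation to error although the design has already removed it from the treatment contrast. The benefit claimed under Design is therefore not delivered under Aim #1. Even when the fallback is used, it adjusts for two communities and not for the events within which women were allocated.

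The second problem is that the analysis of the primary outcome depends on the data. Whether the reader is given crude proportions or model-adjusted proportions, and adjusted for what, is settled after the baseline table has been seen, by a criterion with no threshold. The article does not say which result governs once the fallback has been invoked. At stake are a little power and a primary result with a single definition.

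**Working it through.** **1. Inputs.** From Sample Size and Sample Size Justification: "It is anticipated that 30% of those in the" intervention "group will receive their breast cancer screening within the 120 day study period compared to 15% in the" control group, two-sided α = 0.05, 121 evaluable women per arm. The article gives neither the number and size of events nor the spread of screening rates between them. Those values are assumptions below.

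**2. The plan's own figure.** For the unstratified comparison, with p̄ = 0.225:

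n = [1.960 √(2 × 0.225 × 0.775) + 0.842 √(0.15 × 0.85 + 0.30 × 0.70)]² / 0.15²
= [1.960 × 0.5906 + 0.842 × 0.5809]² / 0.0225 ≈ 2.711 / 0.0225 ≈ 120.5, so 121 per arm.

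Power at 121 is 80.2%. The other Table 5 cells come to 87.1% (stated 87) and 97.7% (stated 97). The sample size was built for the pooled test and reproduces.

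**3. Why the pooled test is conservative.** With arms balanced within strata, the true variance of the difference under the null uses the mean within-stratum variance, while the pooled test uses p̄(1 − p̄) = 0.15 × 0.85 = 0.1275.

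- Strata at 5% and 25%: within-stratum mean (0.0475 + 0.1875)/2 = 0.1175. Ratio 0.1175/0.1275 = 0.922, square root 0.960. True size = P(|Z| > 1.96/0.960) = P(|Z| > 2.04) ≈ 4.1%.
- Strata at 2%, 10% and 33%: within-stratum mean (0.0196 + 0.0900 + 0.2211)/3 = 0.1102. Ratio 0.865, square root 0.930. True size = P(|Z| > 2.11) ≈ 3.5%.

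**4. Power with the planned margins held.** Simulation used 40,000 trials per scenario, 121 per arm and arms balanced within strata. The overall control rate was 15%, and the common odds ratio was chosen so that the overall intervention rate was 30%. The stratified statistic is Cochran-Mantel-Haenszel (CMH), z = Σ(x₁ₖ − Eₖ)/√ΣVₖ, where x₁ₖ is the intervention-arm count in stratum k and Eₖ and Vₖ are its null mean and variance.

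| Assumed control rates | Type I error, pooled / CMH (%) | Power, pooled / CMH (%) |
|---|---|---|
| 2 strata, 15 and 15% | 5.1 / 4.9 | 81.1 / 81.0 |
| 2 strata, 10 and 20% | 4.9 / 5.0 | 80.8 / 81.3 |
| 2 strata, 5 and 25% | 4.3 / 5.1 | 81.9 / 84.7 |
| 10 events, log-odds SD 0 | 5.2 / 5.0 | 80.8 / 80.5 |
| 10 events, SD 0.5 (6.7 to 27.0%) | 4.9 / 5.0 | 81.0 / 81.7 |
| 10 events, SD 1.0 (2.5 to 40.3%) | 3.9 / 5.0 | 82.7 / 85.7 |

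The gap is 0 to about 3 points. With 12 events of 20 women and the same margins, power is 82% against 85% for event rates of 5/25%, and 83% against 88% for 2/10/33%. The widest gap found is thus about 5 points. The pooled test stays above 80% throughout.

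**5. The trigger.** Suppose, for illustration only, that a serious imbalance meant p < 0.05 on any of K independent characteristics. The Demographics section lists seven items, so the chance of switching model under sound randomisation is 1 − 0.95⁷ = 30.2%. Gender cannot vary in this trial; without it the figure is 1 − 0.95⁶ = 26.5%. Simulating that rule with seven characteristics (6,000 null trials in each of two settings) gave a type I error of 4.4% to 4.5%. Taking whichever of the two analyses was significant gave about 5.1%.

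**The case against.** The plan's defenders can say that it names its test, the fallback model type, the class of predictors, the community terms and the fit checks, so it is far from silent. The sample size was computed for the test that is named. Ignoring strata makes the test conservative, so no false claim follows. All of this stands, and it limits the weight of the point.

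The article also states no block scheme, only automatic assignment by the computer program. The conservatism above assumes close balance within each event and would be weaker without it.

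Some stronger readings are tempting but unsupported:

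- **A large loss of power.** A reader who simulates with a fixed within-event odds ratio of 2.43 will see the pooled test fall from 81% to 71% (event rates 5/25%) and 64% (2/10/33%). Most of that fall is a smaller overall effect: the intervention rate drops from 30.0% to 28.0% and 26.8%. The stratified test falls too, to 75% and 70%. Only the gap between the tests belongs here, and those spreads are assumed.
- **Inflated false positives.** A reader might infer this from the data-dependent choice. The check does not show it.
- **A trigger set at p < 0.05.** The 5% remark is made about evaluating the randomisation. The trigger itself has no stated threshold, so the 30% switching rate is only an illustration.

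One rescue fails. The sentence on community indicators might be read as applying to every analysis, but it continues the predictor list of the fallback model, and a 2 × 2 chi-square has no place for such terms. Nor is this a detail left to a fuller plan: the objection is to the test and trigger that the article states.

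**Conclusion.** The point holds in a limited form and should be fixed; it does not threaten the trial. The stated design is stratified by event, the stated primary test is not, and the fallback uses a different stratum and an undefined trigger. The more important defect is that the analysis of the primary outcome is not fixed in advance.

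The cost is small: type I error of about 3.5% to 5%, and 0 to about 5 points of power forgone (0 to 3 in the table). This rests on assumed event numbers and spreads, balance within strata and the planned 15% versus 30%. If events do not differ, nothing is lost. A difference between the two communities is plausible, since Access to Mammography describes different screening routes in each, but the article gives no figure for its size. Neither the 121 per arm nor the 80% power is made wrong.

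**What to change.** - Make the single primary test a Cochran-Mantel-Haenszel test stratified by recruitment event. Pool events below a size fixed in advance within community. Size matters because the recruitment list includes several church events, and small strata are likely.
- Report a Mantel-Haenszel risk difference with 95% CI: Σwₖ(p₁ₖ − p₀ₖ)/Σwₖ, with wₖ = n₁ₖn₀ₖ/Nₖ. Keep the crude 2 × 2 table as description.
- If a logistic model is preferred, always include community terms, or condition on event. Do not treat an unconditional model with a term for every small event as equivalent to the CMH test: with many sparse strata its odds ratio is biased away from 1.
- Delete the serious-imbalance trigger for the primary analysis. Allow covariate-adjusted models only as sensitivity analyses, with the covariates named in advance.
- Apply the same always-stratified rule to Aims 2 and 3, and use one definition of the stratum under Design and Data Analysis.

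The cost is a change of wording. The event is already used to randomise, so no new data or participants are needed and 121 per arm stands. Where strata do not differ, the stratified test gave 80.5% to 81.0% power against 80.8% to 81.1% for the pooled test.

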### Study 2. Randomized Trial

#### Participant Eligibility

Eligibility criteria for randomized trial participation include: individuals must be 40 years of age or older and not up-to-date with breast cancer screening as defined by current American Cancer Society recommendations (see Table 2). Individuals with an acute medical illness or a history of breast cancer will be excluded from the study. Although no formal assessment of dementia or psychiatric illness will be performed, participants demonstrating impaired cognitive function or inappropriate affect or behavior will be excluded from the study. Individuals with another household member enrolled in the study also will be ineligible. Individuals who have been enrolled in the study will not be eligible for repeat enrollment. This is true even if greater than one year has passed since their initial participation. Anyone not eligible for the study but interested in breast cancer screening and information will be given printed self-help materials (*What you need to know about Breast Cancer*, National Cancer Institute, *Breast Cancer and You*, Centers for Disease Control). Participants must have a current, active mailing address and access to a functioning telephone to ensure that the 120 day telephone follow up can be completed.

**Table 2 T2:** Participant Eligibility

Inclusion Criteria	Exclusion Criteria
• Latina or AI/AN woman residing in one of participating communities • Aged ≥40 years of age • Not up to date on mammography screening • Home address & access to a working telephone • Responded to 120-day post randomization follow-up call	• Receipt of mammogram within past year • Acute medical illness, history of breast cancer • Cognitive impairment or inappropriate affect or behavior • Another household member enrolled in the study

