#### Availability of Participants

We will recruit and randomize a total of 290 participants (145 randomized to the **MI**^**2 **^arm and 145 randomized to the **C **arm). Participants will be recruited from annually scheduled and well attended community events in and around the Mayetta and Garden City, KS communities. Garden City is the Finney County seat. Approximately 50% of the county population, and Garden City's population, is non-Hispanic White while 45% of the nearly 41,000 people living in Finney County are Latino (approximately 9,000 Hispanic/Latina females). Our American Indian recruitment in Northeast Kansas will include a five county region; Brown (pop. 10,009/52% female/9% AI/AN); Jackson (pop. 13,240/50% female/7% AI/AN); Doniphan (pop. 7,753/51% female/2% AI/AN); Jefferson (pop. 18,421/50% female/1% AI/AN); and Pottawatomie (pop. 19,695/50% female/1% AI/AN). The AI/AN female population in each county is: Brown = 470; Jackson = 452; Jefferson = 100; Potawatomie = 69; and Doniphan = 58.

Annual community events are common within both target communities. Amongst other events, Mayetta and surrounding areas are home to the Prairie Band Potawatomi Pow Wow (held in June) and Prairie Band Potawatomi Health Fair (September), Kickapoo Pow Wow (July), Sac and Fox Health Fair (September), and the Ioway Health Fair (October). Garden City and its surrounding communities is home to a Cinco de Mayo celebration (May), Community Mexican Fiesta (September), Tyson Health Fair (October), Binational Health Fair (October), and several community events sponsored by the six area churches. Using three CHWs per community, we anticipate being able to recruit approximately 150 women in each community. If, upon a midcourse evaluation, we determine that recruitment is behind schedule, we will supplement our recruitment efforts by partnering directly with health clinics in our target communities to recruit within clinic waiting rooms.

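### Baseline mammography history is collected before randomisation, but the Aim 1 balance check and fallback adjustment cover only demographics and community

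*Protocol article*

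**What the plan says.** **Who is enrolled.** Table 2 (Participant Eligibility) lists "Receipt of mammogram within past year" as the screening-related exclusion. The Aim 1 hypothesis covers overdue and never-screened women together.

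**What is known at baseline.** The section on Prior Breast Cancer Screening Test Utilization describes the items: "Participants will be asked if they have ever been screened for breast cancer and how long ago the test was received". Project Instrumentation says that all measures other than the implementation intentions items are given before randomisation, so both arms have this information.

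**How arms are allocated.** The Design section randomises individuals within each recruitment event. Screening history is not a stratification factor.

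**How balance is examined.** Data Analysis states: "Descriptive statistics will be generated from the sample using the demographic measures". The Demographics section lists gender, education, marital status, age, income, employment and race/ethnicity.

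**How Aim 1 is analysed.** The primary test is a chi-square on a 2 × 2 table. If that baseline description shows serious imbalance, a logistic model follows: "Predictor variables will include the intervention group and the unbalanced demographic characteristics to reduce the impact of such biases". Indicators for community are also included. Aim 3 repeats the same covariate rule for its cumulative logit model.

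**The concern.** A woman 13 months after her last mammogram and a woman who has never had one probably differ in their chance of a mammogram in the next 120 days, whatever the arm. The article's own conceptual-model section names previous experience of the test as something that may matter when a woman is deciding. Past performance of the outcome behaviour is therefore the most obvious baseline predictor, and it is already collected.

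The plan provides a safeguard against chance imbalance but directs it at demographics and community. If one arm happened to receive more recently overdue women, the stated check would not reveal it and the stated model would not correct it. Leaving out a strong predictor also forgoes precision in a trial planned at 80% power with no margin.

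**Working it through.** **1. The plan's own figure.** The sample size section states: "A total of 242 subjects (121 per study arm) would have 80% power to detect the anticipated difference in screening rate between the" two groups, with rates of 30% (MI²) and 15% (C) and two-sided α = 0.05. Using the pooled-variance normal approximation without continuity correction:

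n = [1.96·√(2·0.225·0.775) + 0.842·√(0.15·0.85 + 0.30·0.70)]² / 0.15² = 121 per arm; power at 121 per arm = 80.2%.

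The stated figure reproduces. It uses one blended rate per arm and is not in error on this point.

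**2. How large can a chance imbalance be?** Let w be the share of women recently overdue. The between-arm difference in that share has SD = √(2·w·(1−w)/121).
- w = 0.5: √(0.5/121) = 0.064; 95% limit 1.96 × 0.064 = 12.6 points. An imbalance of 10 points or more has probability of about 12%.
- w = 0.3: √(0.42/121) = 0.059; 95% limit 11.5 points.

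**3. What does it do to the estimate?** Shift = imbalance × (background rate if recently overdue − background rate otherwise). The documents give no such rates, so the splits below are assumptions, each averaging 15% in controls. At 25%/5% in equal halves, a 10-point imbalance shifts the difference by 0.10 × 0.20 = 2 points, and one at the 95% limit by 0.126 × 0.20 = 2.5 points, against the planned 15.

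**4. Power.** Simulated trials at 121 per arm (100,000 or more per row), overall rates fixed at 15% and 30%, constant odds ratio across the two strata. The unadjusted chi-square is compared with a Mantel-Haenszel test stratified on recently overdue versus long overdue or never screened.

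| Control rates (recent / other) | Share recent | Shift at 95% imbalance limit | Power, unadjusted | Power, stratified |
|---|---|---|---|---|
| 20% / 10% | 50% | 1.3 points | 81% | 81% |
| 25% / 5% | 50% | 2.5 points | 81% | 85% |
| 36% / 6% | 30% | 3.5 points | 81% | 88% |
| 28% / 2% | 50% | 3.3 points | 81% | 88% |

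The gain also depends on how the effect is spread over the strata. If 25%/5% becomes 42%/18% under MI² (average 30%), stratified power is 83%. If 35%/5% in a 1:2 mix becomes 54%/18% (again 30%), it is 86%. Unadjusted power is about 81% in both.

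**5. Type I error.** Over all trials it is about 5% for both tests. Among trials whose imbalance exceeds the 95% limit, that of the unadjusted test is about 6% to 14%, depending on the split.

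**The case against.** **Randomisation already protects the test.** This stands. Allocation is individual, so the unadjusted chi-square is a legitimate primary analysis and its error rate already allows for chance imbalance. The standard error of the planned difference is √((0.15·0.85 + 0.30·0.70)/121) = 5.3 points, so a 2-point shift is under 0.4 of a standard error. A reader might infer that the primary result would be biased. The documents do not support that.

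**Screening history is not shut out of the analysis.** This stands in part. Project Instrumentation says in general terms that the instruments are meant to support covariate control of main effects, and nothing forbids the use of screening history. The strong reading, that it can never enter the analysis, goes too far. But that statement names no variable, while the Aim 1 text names its covariates and omits this one.

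**A statistical analysis plan could settle the covariates.** Had the article been silent, this would dispose of the point. It is not silent: it sets a trigger and a covariate rule, and repeats the rule for Aim 3. A plan that added screening history would depart from it.

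**Routine attenders may be screened out.** The section on HLK-BH components counts women who already had an appointment among the ineligible. Table 2 does not repeat this criterion. If applied, it would remove some women likely to attend anyway and make the sharper splits less plausible.

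**Pooling overdue and never-screened women is deliberate.** This stands. The hypothesis is a single pooled one and the sample size serves only the overall comparison. The mixed population is not a defect.

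**Conclusion.** The point holds as a weakness in a covariate rule that the article does fix: as written, an imbalance in screening history is neither looked for nor adjusted for, although the data are in hand before randomisation. What is lost is precision and protection against an unlucky allocation; validity is not affected.

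The size rests wholly on assumed rates by screening history. With a mild split there is practically no power gain. With sharp splits power rises from about 81% to 86–88%, and a chance imbalance at the 95% limit would move the estimate by up to about 3.5 of the planned 15 points. The change is worth making because it costs almost nothing, not because the primary analysis would otherwise be wrong.

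**What to change.** - In Aim 1, prespecify baseline mammography history (for example never; more than 2 years ago; 1–2 years ago) as a covariate or stratum in the primary analysis, whatever imbalance is observed. Include the community or event stratification in the same analysis.
- Use either a Cochran-Mantel-Haenszel test or a logistic model reported as a standardised risk difference. Event-by-history strata may be sparse, so community-by-history strata or the regression model may be more practical.
- Add mammography history to the baseline comparison of the arms.
- Optionally, show separate estimates for never-screened and overdue women, labelled descriptive.

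The cost is a change of wording in the analysis section. The variable is already collected before randomisation in both arms, so no new data and no additional participants are needed.
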